**Methods:**

An investigator-initiated, double-blinded, randomized, placebo-controlled trial is conducted, including 40 patients with CCH. Eligible patients complete a trial with the following elements: I) four weeks of baseline observation, II) 12 weeks of transcutaneous electrical nerve stimulation (TENS) of the occipital nerves, III) implantation of a full ONS system followed by 2 week grace period, IV) 12 weeks of blinded trial with 1:1 randomization to either placebo (deactivated ONS system) or burst (paresthesia-free) stimulation, and V) 12 weeks of tonic stimulation.

The primary outcomes are the reduction in headache attack frequency with TENS and ONS and treatment safety. Secondary outcomes are treatment efficacy of burst versus tonic ONS, the feasibility of TENS as a predictor for ONS outcome, reduction in headache pain intensity (numeric rating scale), reduction in background headache, the patient’s impression of change (PGIC), health-related quality of life (EuroQoL-5D), self-reported sleep quality, and symptoms of anxiety and depression (Hospital Anxiety and Depression Scale, HADS).

Data on headache attack characteristics are registered weekly. Data on patient-reported outcomes are assessed after each trial phase.

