## Methods: Participants, interventions, and outcomes

### Study design

The study is an investigator-initiated, prospective, double-blinded, randomized, placebo-controlled trial.

After an initial baseline period, all participants are treated with TENS. Following the TENS trial all participants are implanted with an ONS system and randomized into one of two arms; one intervention arm and one placebo arm with an allocation ratio of 1:1. The participants in the intervention arm receive burst ONS (paresthesia-free stimulation). In the placebo group, the ONS system will be left turned off. In the final trial phase, all participants cross over to open-label tonic ONS (Fig. 1).

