**Primary endpoints:**
1. 30% reduction in attack frequency with TENS and ONS
2. Safety in ONS and TENS treatment

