### Patient’s Global Impression of Change (PGIC)

PGIC is a single, self-administered tool asking respondents to rate how their condition has changed since a certain point in time [32].

In this study, PGIC is used to record the participants’ self-reported perception of the effect of a given treatment (TENS, burst ONS, and tonic ONS) based on a seven-point scale ranging compared to before the treatment was initiated (baseline).

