### Sample size

Based on our previous experience with ONS treatment [26], we estimate that 50% of the participants who receive active treatment with burst ONS will reach the primary endpoint of a 30% reduction in attack frequency. A blinded trial with burst ONS and placebo has to our knowledge not been carried out earlier, but we hypothesize that no more than 10% in the placebo group will meet the primary endpoint [35]. The sample size is calculated using Fisher’s Exact test based on the above-mentioned assumptions and with 80% power (two-tailed) and a α = 0.05, a total of 40 participants (20 in each allocation group) are needed to be enrolled in the study and an ONS-system implanted.

Each enrolled participant contributes their data regardless of whether they complete the project or not. In case of participants excluded after enrollment, the reason for exclusion will be described.

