### Statistical analysis

Statistical analysis will be conducted by the principal investigator and a statistician blinded for treatment allocation only after follow-up for all participants is completed. No interim analysis will be performed.

Characteristics of the patients will be presented using descriptive statistics to assess if balanced groups were obtained after randomization. The primary analysis will be conducted according to the intention-to-treat principle to avoid introducing bias. In a secondary analysis, a per-protocol analysis will be performed.

The primary outcome is a 30% reduction in attack frequency with TENS and ONS treatment compared to baseline. Relative change in attack frequency (in percent) will be analyzed using the Wilcoxon signed-rank test for paired variables, comparing the baseline data with data from the TENS trial and the trial with burst and tonic ONS, respectively. Because the changes in attack frequency are expectedly skewed [23], a non-parametric test will be applied. In cases with a minimum 30% reduction in attack frequency, sub-analyses will be made to group the treatment responders after relevant cutoffs.

Analysis of the secondary outcomes will be conducted according to the same principle, comparing data from each of the trial phases to baseline using a parametric or non-parametric test for paired variables, depending on the data distribution.

The feasibility of TENS as a predictor for ONS outcome will be evaluated by determining the sensitivity and specificity and calculating the predictive values.

Statistical data analysis will be performed using Stata 17.0 (StataCorp, College Station, USA-TX).

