## Discussion

The effect of ONS on CCH has primarily been evaluated in case series and uncontrolled open-label studies [14–19], aside from a single large dose–response RCT [23]. In the 2023 European Academy of Neurology Guidelines on Cluster Headache [38] there is no recommendation for ONS due to the very low level of evidence. To our knowledge, the study presented here is the first randomized, blinded, placebo-controlled trial on ONS treatment for CCH; when completed, it should constitute a significant contribution to the evidence in the field.

Although little is known about burst stimulation for ONS, there are indications that this type of stimulation also has a preventive treatment effect in CCH patients. Because the participants do not perceive any sensation of stimulation, it enables the conduction of a blinded trial with burst ONS as the active comparator to an inactive placebo treatment.

Burst stimulation was introduced in 2010 and later marketed by neuromodulation device manufacturer Abbott as BurstDR. Subsequently, other manufacturers of neuromodulation systems have developed similar waveforms marketed under other burst labels. A difference in mechanism of action has been claimed [39], however, in this study we do not distinguish between the different variations of the burst waveforms.

The study design allows a comparison between burst ONS and placebo and enables a head-to-head comparison of the efficacy of burst and tonic ONS. In addition, by comparing the effect of treatment with TENS and tonic ONS, respectively, it is possible to evaluate whether the effect of TENS can be used as a feasible preoperative screening tool for ONS outcomes and can be used to select the most eligible candidates for implantation.

There is no official consensus about optimal stimulation settings in ONS for CCH. The study will provide important information about the efficacy of burst ONS and explore whether the addition of this stimulation paradigm might help improve future stimulation protocols.

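### The sample size rests on a burst-versus-placebo Fisher test, but the stated analysis is paired against baseline and names no between-arm test

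*Protocol article*

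**What the plan says.** The design is a parallel comparison. The abstract describes "12 weeks of blinded trial with 1:1 randomization to either placebo (deactivated ONS system) or burst (paresthesia-free) stimulation", and the Study design section confirms "one intervention arm and one placebo arm with an allocation ratio of 1:1".

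The Sample size section takes the endpoint as a 30% reduction in attack frequency. It expects half of the burst group to reach it, and for the other arm states that "we hypothesize that no more than 10% in the placebo group will meet the primary endpoint". With Fisher's exact test, two-tailed, 5% alpha and 80% power, it arrives at 20 per group.

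The Statistical analysis section restates the 30% endpoint but then analyses relative change in percent. The test is a Wilcoxon signed-rank test for paired data, "comparing the baseline data with data from the TENS trial and the trial with burst and tonic ONS, respectively". Secondary outcomes follow the same principle, "comparing data from each of the trial phases to baseline using a parametric or non-parametric test for paired variables". The Outcome measures section gives the same general rule of comparing each phase with baseline. The only between-group statement in the Statistical analysis section is a descriptive check of balance after randomisation.

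Table 4 words the primary efficacy endpoint as "30% reduction in attack frequency with TENS and ONS". The Discussion says that "The study design allows a comparison between burst ONS and placebo" but gives no test for it.

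**The concern.** The Sample size section needs two independent groups and a binary outcome. The stated analysis uses one group at a time and a continuous outcome. They answer different questions, and only the first uses the randomisation and the blinding.

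The four-week baseline comes before 12 weeks of TENS, the implantation and the grace period. A burst-versus-baseline difference therefore combines any burst effect with natural fluctuation, carry-over from TENS, effects of surgery and placebo response. The placebo arm exists to remove these, and the stated analysis does not call on it. All 40 participants receive an implant so that this contrast can be made. A positive paired result could be read as placebo-controlled evidence when it is not.

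The same gap affects the secondary outcomes. PGIC shows it most plainly: it records the "self-reported perception of the effect of a given treatment (TENS, burst ONS, and tonic ONS") as a change since baseline, so there is no baseline score to pair with, and placebo is not among the treatments listed.

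**Working it through.** **1. The two sections side by side**

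| | Sample size section | Statistical analysis section |
|---|---|---|
| Comparison | burst vs placebo | each of TENS, burst and tonic vs baseline |
| Outcome | responder, at least 30% reduction | relative change in percent |
| Test | Fisher's exact, two independent groups | Wilcoxon signed-rank, paired |
| Placebo arm | supplies the 10% | not named |

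Fisher's exact test appears only in the left-hand column's section.

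**2. The plan's own figure**

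Inputs from the Sample size section: p1 = 0.50, p2 = 0.10, two-sided alpha 0.05, power 80%, 20 per arm.

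The uncorrected two-proportion formula, with mean proportion 0.30, gives

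n = [1.96 × √(2 × 0.30 × 0.70) + 0.842 × √(0.50 × 0.50 + 0.10 × 0.90)]² / 0.40² = (1.270 + 0.491)² / 0.16 ≈ 19.4, so 20 per arm (81.3% power).

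So 40 is reproduced by a chi-square approximation. For the two-tailed Fisher test that the text names, power is the sum over all outcomes (a, b) of Bin(a; n, 0.50) × Bin(b; n, 0.10), counting those with Fisher p ≤ 0.05:

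| n per arm | power |
|---|---|
| 20 | 74.2% |
| 22 | 78.6% |
| 23 | 81.1% |

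Reaching 80% takes 23 per arm, 46 in total.

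**3. What the paired test would do with no burst effect**

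The documents give no shared fall and no variance, so everything here is assumed: 20 per arm, mean 28 attacks per four weeks, Poisson counts, between-patient log-SD 0.5, independent log-SD of 0.2 to 0.4 in baseline and in phase, a four-week baseline and a 12-week phase. Both arms have the same fall. Ranges run over the log-SD.

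| Shared fall | Paired, percent change | Paired, raw counts | Between arms |
|---|---|---|---|
| 0% | about 8% | about 5% | about 5% |
| 10% | 6–11% | 9–21% | about 5% |
| 20% | 13–49% | 28–70% | about 5% |
| 30% | 39–90% | 61–97% | about 5% |

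Percent change from a noisy baseline is skewed upward, which is why that column is not exactly 5% with no fall and dips at small falls.

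A second model with normally distributed percent change and an SD of 30 points gives 28% at a 10% shared fall and 79% at 20%, with the between-arm test at about 4–5%. The two models agree on direction but not on size.

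**The case against.** **The article is condensed, and a fuller plan may contain the test.** That is possible, and the Abstract and the Discussion show that a burst-placebo comparison is intended. A reader might infer that it will never be tested; the documents do not show that. But the Statistical analysis section is not silent: it names the test, the pairing and the comparisons. A fuller plan with a between-arm test would contradict this text, so the two need reconciling either way.

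**Table 4 is only a list of endpoints.** This stands. Such a list need not name a comparator, and the Sample size section applies the first entry to both arms. The point does not rest on Table 4.

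**The simulated error rates rest on generous shared falls.** This also stands. In the first model, a 20% fall makes about 35–41% of placebo patients responders and a 30% fall about half, against the plan's ceiling of 10%. The rates illustrate a direction and are not estimates for this trial.

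**Three stronger readings are tempting and should not be taken.**

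- A family-wise error of 14.3% (1 − 0.95³) assumes three independent tests, but these share patients and a baseline. They concern different interventions, and alpha control is commonly left to an analysis plan.
- The entry threshold of 15 attacks per month might suggest marked regression to the mean. The documents do not say how the threshold is ascertained. If selection precedes the four-week baseline, much of that regression has already happened.
- TENS and tonic need not lose their endpoint status. The plan makes TENS primary deliberately, and naming a burst-placebo test resolves the contradiction.

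A one-sample test of PGIC against no change would avoid the pairing problem, but it would still not compare the arms.

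**Conclusion.** The point holds as an internal contradiction. The trial is sized for a between-arm test of responders, and the stated primary analysis is a within-patient test of percent change that leaves the randomised contrast without a named test. This follows from the text alone and needs no assumption.

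How often it would mislead cannot be fixed from the documents. Under the first assumed model, false positives on percent change are modest at a 10% shared fall and can approach one half at 20%. A between-arm comparison stays near 5% because a fall common to both arms cancels.

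It should be corrected before unblinding, because it decides whether the trial's main conclusion is placebo-controlled.

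**What to change.** In the Statistical analysis section:

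- Name burst versus placebo over the blinded 12-week phase, in all randomised participants, as the confirmatory efficacy analysis. Use the Sample size endpoint (at least 30% reduction from baseline) and a two-tailed Fisher's exact test.
- Compare the secondary outcomes between arms at the end of that phase, with PGIC analysed directly as a change rating.
- Keep the TENS and tonic comparisons with baseline, labelled as uncontrolled and outside the placebo-controlled claim.

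In the Sample size section, replace the 80% by 74.2% for 20 per arm at 50% versus 10%. Keeping 80% with this test would take 46 participants, six more than planned.

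The analysis change itself is wording. It needs no new data, and it can be made while the blind is intact: the plan keeps it until every participant has finished the final phase and analyses nothing before then. The cost is an openly lower power figure, and a burst claim that depends on the between-arm result.

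### The signed-rank test is set on percent change from baseline, a scale that is not symmetric when nothing has changed; the resulting error is modest and conditional, and one sentence removes it

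*Protocol article*

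**What the plan says.** The Statistical analysis section of the Protocol article fixes the scale and the test for the primary outcome: "Relative change in attack frequency (in percent) will be analyzed using the Wilcoxon signed-rank test for paired variables". The same sentence goes on: "comparing the baseline data with data from the TENS trial and the trial with burst and tonic ONS, respectively". The reason for the test follows: "Because the changes in attack frequency are expectedly skewed [23], a non-parametric test will be applied". It is the only test named for the primary outcome, and it serves the TENS, burst and tonic comparisons alike. The article gives neither an SD nor the direction of the expected skew, and it does not mention symmetry.

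The only quantitative hint about patient-level variability is in the Sample size section, which assumes that "50% of the participants who receive active treatment with burst ONS will reach the primary endpoint of a 30% reduction in attack frequency" and that "no more than 10% in the placebo group will meet the primary endpoint". The Abstract gives a 4-week baseline and 12-week treatment phases. Table 3 requires at least 15 attacks per month.

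**The concern.** The signed-rank test ranks the absolute changes and compares the rank sums of rises and falls. Under no effect it needs each change to be as likely to be +x as -x. Percent change fails this even when baseline and follow-up are exchangeable. A patient going from 20 to 60 attacks scores +200%, and one going from 60 to 20 scores -67%. The two are mirror images, but the rise always takes the higher rank. The baseline is also the noisier of the two measurements (4 weeks against 12) and sits in the denominator, which stretches the upper tail further.

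Skewness is therefore no reason to trust this test on this scale. At stake are an excess of nominally significant worsening and a loss of power to show improvement. The loss matters most for burst, where only about 20 patients contribute.

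**Working it through.** **The plan's own figure.** No figure in the article rests on this test. The sample size ("The sample size is calculated using Fisher’s Exact test based on the above-mentioned assumptions"; 20 per group) compares responders between groups, so nothing below changes it. For the record, two-sided Fisher power for 50% v 10% is 74.2% at 20 per group, and 80% needs 23 per group (81.1%). The uncorrected chi-square formula does give 20 per group. That is a separate matter.

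**Inputs from the article.** Two-sided alpha 0.05, so 2.5% in each direction; n=20 (burst) and n=40 (TENS, tonic); windows of 4 and 12 weeks; at most 10% of placebo patients with a 30% reduction.

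**Assumed, because the article does not give it.** The within-patient variability. It is set so that the share of 30% reductions with no effect is close to 10%.

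**Test statistic.** z = Σ sign(d)·R / √Σ R², where R is the rank of |d|; reject if |z| > 1.96. For baseline rate B and phase rate F, three versions of d are compared: percent change (F - B)/B, raw difference F - B, and log ratio ln(F/B), with a small constant added in the count models.

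**Model 1: exchangeable log-normal pairs.** A 30% reduction with no effect has probability Φ(ln 0.7 / s). Setting this to 0.10 gives s = ln(1/0.7)/1.2816 = 0.3567/1.2816 = 0.278.

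**Model 2: Poisson counts.** About 7 attacks a week, 4-week baseline, 12-week phase, phase log-SD 0.1. About 8% reach a 30% reduction with no effect.

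**False worsening on percent change, no effect, no selection on baseline (nominal 2.5%)**

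| | n=20 | n=40 |
|---|---|---|
| Model 1 | 4.2% | 5.7% |
| Model 2 | about 5% | about 7-8% |

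In Model 1 false improvement is 1.4% (n=20) and 1.0% (n=40), while raw differences and log ratios stay near 2.5% each way. In count models with unequal windows the raw difference stays closest to nominal, and the log ratio keeps a small part of the excess. With autocorrelated weekly counts and 13.7% responders under no effect, false worsening at n=20 is 6.9% (percent), 3.1% (raw) and 4.0% (log).

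**Power to show improvement, n=20**

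| True effect | Percent | Raw | Log ratio |
|---|---|---|---|
| Uniform 30% fall, Model 2 | 98% | 100% | 100% |
| Half respond with a 60% fall, Model 2 | about 78% | about 83% | about 88% |
| Uniform 15% fall, Model 1 | 57% | 67% | 67% |

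**Sensitivity to variability.** With a 30% median fall at n=20 (log-normal pairs), power on percent, raw and log scales is 99/100/100% at log-ratio SD 0.3, 67/79/84% at 0.5 and 32/51/56% at 0.7. The loss grows with variability.

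**Selection on baseline.** If the threshold of 15 attacks is applied to the same 4-week count (log-normal pairs, SD 0.3, n=20, no effect), false worsening / false improvement become 2.2/2.4% (percent), 1.6/3.4% (raw) and 1.2/4.1% (log).

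**The case against.** Four objections deserve a hearing.

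*Reading.* A signed-rank test for paired variables that sets baseline data against phase data could mean that paired frequencies are ranked and percent change only expresses the result. On that reading the bias is largely absent. This stands as a doubt, but the sentence names relative change in percent as what is analysed, so the text needs correcting either way.

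*Size.* A reader might infer much larger harm, such as false worsening of 9-16% at n=40 or power falling to single figures. Those results need a phase log-SD of 0.2 to 0.5, which implies about 16% to 32% responders with no effect. The article assumes at most 10% on placebo, so it does not support them.

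*Direction.* A reader might infer that the analysis is always tilted toward worsening. That holds only without selection on the baseline count. If entry is judged on that count, regression to the mean pushes toward improvement and offsets or reverses the tilt, and the log ratio then suffers most. The article does not say whether the baseline count decides entry. This is a separate problem on every scale, and two errors that happen to cancel do not justify the test.

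*Consequence.* Without selection, the error is conservative for claiming benefit, and large uniform effects would be found regardless. Both are true. Neither removes the loss when only some patients respond, which is the pattern the article's own 50% responder assumption suggests.

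**Conclusion.** The point holds in a limited form. As written, the plan pairs the signed-rank test with a scale that breaks its symmetry requirement and offers skewness as the justification. The skew the article expects does not itself prove asymmetry under no effect; the percent scale creates it.

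At a variability compatible with the article's placebo assumption, false worsening is roughly double to triple the nominal 2.5%. For a mixed response, power at n=20 falls by about 5 points against raw paired rates (83 - 78) and about 10 against the log ratio (88 - 78). For a uniform 30% fall the loss is about 2 points.

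These figures rest on an assumed SD calibrated to a hypothesised 10%, on the percent-change reading of the sentence, and on no selection by the baseline count. The sample size of 40 is not affected.

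**What to change.** State in the analysis plan, before unblinding, that the signed-rank test is applied to each patient's paired attack rates (baseline v phase), or to their log ratio. Keep percent reduction for description and for the 30% responder definition.

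Raw paired rates need no constant for zero counts, fit the existing wording and stay closest to nominal size. The log ratio has more power when responses are mixed, and its result can be reported as a ratio with a 95% CI. It does need a stated constant for attack-free patients, and it is the most exposed to regression to the mean if entry depends on the baseline count. The same sentence could say whether that count is used for entry. A t-test on percent change is not a remedy: with no effect, at log-ratio SD 0.5 and n=20, its false worsening is 9%, against 5.7% for the signed-rank test on that scale.

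The cost is one sentence, with no new data, patients or visits. The downside is that the test no longer uses the percent scale on which the endpoint is reported.

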**Fig. 2 Fig2:**
[figure not shown]
Outcome parameters in correlation to trial phases and study visits. TENS, transcutaneous electrical nerve stimulation. ONS, occipital nerve stimulation. PGIC, patient's global impression of change. HADS, hospital anxiety and depression scale. EuroQoL-5D, European Quality of Life – 5 Dimensions

All questionnaires are electronic and are entered via a personal link sent automatically by e-mail. If the headache registrations and questionnaires are not completed within 24 h, an e-mail reminder is generated.

The data collected during each trial phase will be compared to the baseline and analyzed in order to evaluate the study endpoints listed in Table 4.

**Table 4 Tab4:** Study endpoints

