**Secondary endpoints**
1. Participant’s assessment of treatment effect evaluated by PGIC-score
2. Treatment efficacy of burst versus tonic ONS as a preventive treatment for chronic cluster headache
3. Feasibility of TENS as a predictor for the outcome of ONS treatment
4. 30% reduction in pain intensity
5. Quality of life as evaluated with the EuroQoL-5D questionnaire
6. Reduction in background headache
7. Self-reported sleep quality
8. Symptoms of anxiety and depression as evaluated by HADS

*TENS* Transcutaneous electrical nerve stimulation, *ONS* Occipital nerve stimulation, *PGIC* Patient's global impression of change, *HADS* Hospital anxiety, and depression scale, *EuroQoL-5D* European Quality of Life – 5 Dimensions

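### For pain intensity, EQ-5D, background headache, sleep and HADS the plan states only paired tests against baseline, so the blinded phase has no stated burst-versus-placebo comparison

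*Protocol article*

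**What the plan says.** The Statistical analysis section states that "Analysis of the secondary outcomes will be conducted according to the same principle" as the primary analysis, and then spells this out as "comparing data from each of the trial phases to baseline using a parametric or non-parametric test for paired variables, depending on the data distribution". The primary rule that is copied is a Wilcoxon signed-rank test "comparing the baseline data with data from the TENS trial and the trial with burst and tonic ONS, respectively". Placebo is not among the conditions it lists. The Outcome measures section gives the same rule for everything in Table 4: "The data collected during each trial phase will be compared to the baseline and analyzed in order to evaluate the study endpoints".

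Five secondary endpoints in Table 4 are at issue: "30% reduction in pain intensity" (endpoint 4), "Quality of life as evaluated with the EuroQoL-5D questionnaire" (endpoint 5), background headache (6), sleep quality (7) and HADS (8).

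The design is a different matter. The Study design section describes "one intervention arm and one placebo arm with an allocation ratio of 1:1", with 12 weeks of blinded follow-up. The Abstract gives burst against placebo as part of the aim, and the Discussion says the design permits that comparison. The Sample size section computes 20 per group from a two-group Fisher's exact test of responder proportions.

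**The concern.** The named test does not answer the question that the randomisation was set up to answer. A paired comparison with baseline estimates the change over time in whoever is tested. It does not estimate the difference between burst and an inactive device.

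The baseline is the four-week observation period, before 12 weeks of TENS, the implantation and the two-week grace period. A change from that baseline to the blinded phase can therefore contain regression to the mean (entry requires at least 15 attacks a month), carry-over from TENS, effects of surgery and attention, and natural course. All of these can occur in both arms. The placebo arm is there to remove them, and the stated rule does not use it for endpoints 4 to 8. At stake is whether any statement about burst stimulation on pain, quality of life, sleep, background headache, anxiety or depression rests on a randomised comparison.

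**Working it through.** **What the stated rule can test in the blinded phase**

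- The secondary rule compares a phase with baseline by a paired test. The text does not say whether the two arms are kept apart.
- Reading 1, the more natural: the rule follows the primary analysis, which names burst and tonic stimulation separately. The burst arm (n = 20) is tested against its own baseline.
- Reading 2: the phase is taken as a whole, so both arms (n = 40) enter one paired test.
- Neither reading yields a test of burst against placebo.

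**The plan's own figure**

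The article gives no SD, effect size or power for endpoints 4 to 8, so there is no figure to reproduce on this point. The one calculation it reports (50% versus 10% responders, 20 per arm) concerns the attack-frequency responder endpoint. It is used here only for the group size.

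**Size of the problem under an assumed range**

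Inputs: 20 per arm (Sample size section) and two-sided alpha 0.05 (same section). Assumed: normally distributed changes, a true burst-placebo difference of zero, and the same mean change d in both arms, with d in units of the SD of change. Because the documents give no value for d, a range is shown.

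For the paired t test, the chance of significance is P(|T| > t) with T non-central t on n - 1 degrees of freedom and non-centrality d × √n. For n = 20, √20 = 4.47 and the critical value is 2.093. The non-centralities are 0.2 × 4.47 = 0.89, 0.3 × 4.47 = 1.34, 0.5 × 4.47 = 2.24 and 0.8 × 4.47 = 3.58. The exact chances are 13.6%, 24.7%, 56.5% and 92.4%. Simulation of 20,000 trials agrees (Wilcoxon on 3,000 of them):

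| Shared change d (SD of change) | Burst arm, paired t, n = 20 | Burst arm, Wilcoxon, n = 20 | Both arms as one phase, n = 40 | Between-arm t test of change |
|---|---|---|---|---|
| 0.2 | 14% | 12% | 24% | 5% |
| 0.3 | 25% | 24% | 46% | 5% |
| 0.5 | 56% | 53% | 87% | 5% |
| 0.8 | 92% | 91% | >99% | 5% |

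**Testing each arm separately**

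If the placebo arm were also tested against baseline, exactly one of the two arms would be significant in 2p(1 - p) of trials. At d = 0.5 this is 2 × 0.56 × 0.44 = 49%, and the simulation gives 49%. Half of these cases would show burst significant and placebo not, with no difference between them.

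**The case against.** The strongest counter-argument is that the article repeatedly states the intention to compare burst with placebo, sizes the trial for two groups and does not say that the paired tests are the only ones. It condenses a fuller protocol, and an analysis plan may exist. This limits the claim but does not remove it. Detail left to another document would be no finding. Here, however, the article does state a method for these outcomes, and that method cannot deliver the stated aim. An analysis plan would have to override it.

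Two stronger readings are tempting and are not supported. A reader might infer that burst and placebo participants will be pooled in one test. The text does not say so, and the primary rule it copies lists burst by name, which points to a burst-only test. The n = 40 column above therefore covers a less natural reading and should not carry the argument. A reader might also infer that the investigators will report any change from baseline as proof of burst efficacy, or that the arms will never be compared. No section says either. The supportable statement is a mismatch between aim and named test.

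Three further points stand:

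- The size rests on assumed values, and it varies widely with the shared change.
- Only EQ-5D and HADS are collected at the end of each phase. Pain, background headache and sleep come from the weekly registration, so a single end-of-phase value does not exist for them.
- One ANCOVA would not suit a 30% responder endpoint or a symptom recorded as present or absent.

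Paired tests are also reasonable for the TENS and tonic phases, which have no concurrent control.

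**Conclusion.** The point holds as a mismatch that needs correction. For secondary endpoints 4 to 8 the article names only paired comparisons with a baseline that precedes TENS and surgery. It states no comparison between the randomised arms in the blinded phase, contrary to its own aim. On the burst-arm reading, and with no true burst-placebo difference, a significant result would appear in about 14% of trials for a shared change of 0.2 SD of change, rising to 92% at 0.8 SD, against about 5% for a between-arm test. These figures assume 20 per arm, normal changes and an equal mean change in both arms. The direction of the problem does not depend on those assumptions, but its size does, and the documents do not allow it to be fixed more closely.

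The same paired rule is stated for the primary attack-frequency analysis, so the fault is not confined to these endpoints.

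**What to change.** For the blinded phase, replace the paired rule with a comparison of burst with placebo by intention to treat, adjusted for the baseline value and reported with a 95% CI:

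- **EQ-5D and HADS:** ANCOVA of the end-of-phase score on arm and baseline score.
- **Pain intensity:** a blinded-phase summary of the weekly ratings, as a baseline-adjusted difference in mean NRS, together with a between-arm comparison of the proportion reaching the 30% reduction.
- **Sleep quality:** an ordinal model for the four-point weekly scale.
- **Background headache:** a binary model, or a model for the proportion of weeks with background headache.

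Keep paired phase-versus-baseline results as description in the blinded phase, and for the single-group TENS and tonic phases. Correct the primary attack-frequency analysis in the same way, so that the two rules stay consistent.

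The cost is revised wording, a defined weekly summary for three endpoints and one model per endpoint. No new data are needed. The between-arm test will show how limited the precision is: with 20 per arm, an unadjusted t test of change has 80% power only for a difference of about 0.91 SD of change. These results should therefore be read through their confidence intervals.
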